### Sampling frame

About seven acute coronary syndrome (ACS) patients are admitted to the acute general hospital per week, including unstable angina, non-ST and ST-segment elevation ACS. About 40% will present with premature ACS [4]. Maltese individuals who are 30 years and older often have quite extensive families. Across 52 weeks (1 year), logistically, if every patient informs their relatives, this would amount to over 100 eligible participants. Since there are no records concerning the recruitment uptake and attrition rate, we will dedicate two years for recruitment and data collection. A sample of 100 participants should be adequate to prove that the process is viable. As the pilot study is not expected to be powered to detect differences between groups, there is no universally accepted calculation for the pilot study sample size [38]. If a meaningful group difference is unknown and the pilot study is intended to establish an effect size for sample size calculation, it is recommended to have 30 to 40 participants recruited in each group. Recommendations for feasibility studies propose a minimum of 30 participants per arm to estimate parameters for future sample size calculations [39, 40]. Ultimately, the sample size decision for a pilot RCT must also consider the research timeline, human resources and costs, and the research objectives [40, 41].

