#### Group randomisation

Before the baseline/pre-intervention evaluation, approximately 100 participants shall be randomly allocated to one of the two groups:
The intervention group shall consist of 50 participants. Participants in this group will have one face-to-face session (evaluation of modifiable risk factors, 2-way risk factor communication, education, and individualised counselling to set up a cardio-protective documented plan) followed by weekly telephone-based cardio-protective reinforcement sessions for up to 12 weeks.The control group shall consist of 50 participants. Participants will have one face-to-face session of verbal lifestyle advice only.

Block randomisation will be applied to balance out the sample size between the intervention and control groups. An opaque sealed envelope technique, using block randomisation with blocks of size four, will be implemented for this study. This method will allow an equal chance of being allocated to one of the two groups and ensure that near-equal numbers are assigned to each group, minimising the risk of group imbalances and allocation bias.

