#### Follow-up

Participants will be assessed at the same time points after being recruited in the study. Follow-up points for study participants translate into the following phases: baseline/pre-intervention, 6 months, and 12 months after baseline/pre-intervention. Table 4 shows data collection points.

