#### Secondary outcome analysis

##### Objective 3: Estimates of effect and preliminary evidence of efficacy

The likely range of effects will be estimated using liberal confidence intervals. Preliminary estimates of intervention efficacy will be established via hypothesis tests with liberal alpha values (e.g. 0.15, 0.2). Numerical outcomes measured on an interval level, and numerical outcomes measured on an ordinal scale that can be considered approximate to interval level, will be assessed using independent samples t tests. Categorical data will be assessed using the chi-squared test for association.

Intention-to-treat analysis will be used to test for the differences between the two groups at the endpoint [50]. Intention-to-treat analysis is considered the gold standard method for evaluating a new intervention. This method includes all study participants whether or not they have completed the study program and will preserve the randomisation process as it keeps the groups balanced in their number of participants in case of any drop-outs, thus minimising biases [51].

Risk ratios (RRs) will be generated for selected outcome variables, dichotomised as necessary, from proportions of participants meeting particular criteria (e.g. control of blood pressure) in the control and intervention groups.

Effect sizes such as Cohen's d statistics will be calculated for each outcome measure and presented alongside parameter estimates in each group and associated confidence intervals. These, in conjunction with other statistics derived from the pilot analysis, may be used to estimate sample size for a subsequent follow-up RCT [38].

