### Counterbalancing for confounding factors and bias

There are several possible interacting variables: age, health literacy, educational levels, isolation, employment, sex, psychometric scales, time of the cardiac patient event, and family clustering effects. These multiple variables make it rather complex to decide on stratified sampling. Additionally, as the sample solely depends on the recruitment process, an element that still needs to be tested, it was decided not to stratify at this phase.

The chosen method to generate the allocation sequence should produce comparable groups. However, due to a lack of resources, allocation concealment is not possible. This study is single-blinded, where participants will only be informed about the aim of the study but not about being part of an intervention or control group. However, the researcher will be aware of which participants have been allocated to the intervention group. Thus, there is a risk of performance and detection bias. An independent person from the study will perform group allocation. Also, group allocation will take place before the baseline risk assessment. Using these methods will avoid any attempt to allocate participants to the Intervention according to their risk profile. This step is necessary when the study's nature does not allow proper blinding [56].

Numbers of the total sample randomised, those lost to follow-up, and reasons for withdrawal will be recorded for each group. The risk of attrition bias will be minimised by carrying forward the last observation. This method will keep the groups balanced if there is a loss to follow-up/missed measuring time points.

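### Carrying the last observation forward does not minimise attrition bias, as the protocol states; it can bias the 12-month effect in either direction

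*Protocol article*

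**What the plan says.** The section on counterbalancing for confounding factors and bias gives the only missing-data rule in the article: "The risk of attrition bias will be minimised by carrying forward the last observation". It adds: "This method will keep the groups balanced if there is a loss to follow-up/missed measuring time points".

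Under Objective 3, intention to treat is defended by a similar argument about numbers: it "keeps the groups balanced in their number of participants in case of any drop-outs, thus minimising biases". That sentence concerns the analysis set, not carrying forward, but it treats equal numbers as protection against bias in the same way.

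Four other statements determine what the rule would do:

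- Follow-up section: outcomes are measured at "baseline/pre-intervention, 6 months, and 12 months after baseline/pre-intervention". A missing 12-month value is therefore filled with the 6-month value, or with baseline if 6 months is missing too.
- Group randomisation section: the face-to-face intervention session is "followed by weekly telephone-based cardio-protective reinforcement sessions for up to 12 weeks".
- Sampling frame section: attrition is unknown ("Since there are no records concerning the recruitment uptake and attrition rate").
- Objective 3: numerical outcomes are compared by independent-samples t tests, and Cohen's d with other pilot statistics may be used to size the next trial.

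**The concern.** The stated reason does not support the conclusion. Carrying values forward keeps 50 against 50 in the analysis, but bias from attrition arises when the substituted values differ on average from what the leavers would have shown at 12 months. Equal counts say nothing about that.

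The design gives two routes to such a difference. A participant lost before 6 months is given no change. A participant lost after 6 months is given a value from about 3 months after the last call, while the endpoint lies about 9 months after it. The two routes can push the estimate in opposite directions.

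At stake are the secondary effect estimates, their confidence intervals, and a Cohen's d that may set the size of the definitive trial. Filled values also enter the t test as measured ones, so the intervals claim more information about 12 months than was collected.

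**Working it through.** The plan gives no figure to reproduce on this point. It states no dropout, SD, effect size or power, and its total of 100 is a feasibility number.

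**Inputs from the protocol.** 50 per arm; visits at baseline, 6 and 12 months; calls for up to 12 weeks; t tests; Cohen's d as a possible planning input.

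**Assumed inputs.** True 12-month effect *d* = 0.50 SD; no change in controls; equal SD at each visit; dropout unrelated to outcome. Let *m* be the share missing at 12 months, *q* the share of those also missing at 6 months, and *h* the ratio of the 6-month to the 12-month effect. The next trial is taken at two-sided alpha 0.05 and 80% power.

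**Step 1: effect after carrying forward.** Expected effect = *d*[(1 − *m*) + *m*(1 − *q*)*h*].

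- All leavers go before 6 months (*q* = 1), *m* = 0.20: 0.50 × 0.80 = 0.40. For *m* of 10%, 30% and 40%: 0.45, 0.35 and 0.30.
- All leavers have a 6-month value (*q* = 0), *h* = 1.3, *m* = 0.20: 0.50 × (0.80 + 0.26) = 0.53. For *m* of 10% and 30%: 0.515 and 0.545.

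**Step 2: consequence for the next trial.** By the normal approximation to the t test, n per arm = 2(1.96 + 0.84)²/*d*² ≈ 15.7/*d*².

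| *d* used for planning | n per arm | Real power if true *d* = 0.50 |
|---|---|---|
| 0.50 | 63 | 80% |
| 0.40 | 99 | 94% |
| 0.53 | 56 | about 75% |

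**Step 3: unequal loss with no true effect.** Suppose both arms drift by 0.2 SD, and 30% of one arm and 10% of the other leave before 6 months. The filled means then differ by 0.2 × (0.70 − 0.90) = −0.04 SD, a small difference created by the method alone.

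**Step 4: precision.** With 20% missing, 40 of 50 per arm are measured at 12 months. Counting 50 makes the standard error √(40/50) = 0.89 of what the measured values alone would give.

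**Step 5: correlation with baseline, if anyone takes it from the filled data.** Let *r* = 0.6 be the true correlation of baseline with 12 months and 0.7 that of baseline with 6 months (both assumed). If 20% carry baseline, it becomes 0.80 × 0.6 + 0.20 = 0.68. If 20% carry 6-month values, it becomes 0.80 × 0.6 + 0.20 × 0.7 = 0.62. The first changes the baseline-adjusted sample size by (1 − 0.68²)/(1 − 0.6²) = 0.84. The same carry-forward also shrinks the effect to 0.8 of its true value, which multiplies n by 1/0.64 = 1.56. The net factor is 1.56 × 0.84 = 1.31.

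**Step 6: check of the alternative.** In simulations with 200,000 per arm, baseline-adjusted analysis of observed data returned 0.49 to 0.50 when dropout was random or depended on baseline. When dropout depended on the 6-month result and differed by arm, the same analysis without the 6-month value gave 0.45 to 0.55. The 6-month value therefore belongs in the model.

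**The case against.** The primary objectives are feasibility and acceptability, and carrying forward affects neither. Efficacy is secondary, preliminary and unpowered; the pilot statistics only may be used for sizing; and losses with reasons are to be recorded by group, so attrition will be visible. All of this stands, and it limits the severity.

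Carrying forward is also harmless for the mean difference in some cases: no missing data, leavers who truly stay at the carried value, or no true effect with equal dropout unrelated to outcome. With attrition unknown, none of these can be excluded, but none can be relied on.

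A reader might infer three stronger claims that the documents do not support.

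- *The bias has a known direction or is large.* Overstatement needs an effect that fades between 6 and 12 months. The article reports no trajectory, and the intervention participant's report is updated at 6 and 12 months, so contact does not end entirely at week 12. At *h* = 1.3 the overstatement is only 3% to 9% for 10% to 30% missing.
- *The next trial would be too small because the correlation with baseline is inflated.* The article does not name that correlation as an output and plans unadjusted t tests. If baseline values are carried and both the effect and the correlation come from the pilot, Step 5 shows a trial about 31% too large.
- *Loss will differ between arms.* The contact burden differs (one session plus 12 calls against one session), so this is plausible, but nothing in the article establishes it. The illustrations in Steps 1 and 2 do not depend on it.

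**Conclusion.** The statement that carrying forward minimises attrition bias is wrong as written, and it is current text rather than a detail left to an analysis plan. The method can bias the 12-month effect and Cohen's d in either direction, and it makes confidence intervals overstate the information.

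On the stated assumptions, 20% missing turns a true 0.50 SD into anything from 0.40 to 0.53 SD, depending on when people leave. A next trial planned from those figures would have 99 or 56 per arm where 63 are needed. These numbers show what is possible; they do not predict what will happen. Inflation of the correlation with baseline is a side issue that matters only if the next trial adjusts for baseline. Severity: should be fixed.

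**What to change.** 1. Delete the statement that carrying forward minimises attrition bias, and the balance argument attached to it. Keep carrying forward at most as a sensitivity analysis.
2. For numerical outcomes, analyse all observed 6- and 12-month values by allocated arm in a linear mixed model for repeated measures, with arm, visit, arm-by-visit, baseline and baseline-by-visit as terms. Baseline enters as a covariate and not also as a response. Participants with neither follow-up value add nothing to this model, so report their number by arm.
3. For smoking and the dichotomised outcomes, use multiple imputation by arm that includes the baseline and 6-month values.
4. Add one sensitivity analysis that imputes missing values and shifts those in the intervention arm towards no benefit over a range stated in advance, with the direction set outcome by outcome.
5. Estimate SDs, any correlations and attrition for the next trial from observed data only.

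The cost is a change of analysis wording and a little more analysis work. No new data, visits or participants are needed.

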## Conclusions

This research will provide new knowledge about the feasibility of the processes and inform the intervention components' acceptability by siblings and offspring. The Intervention may provide a new preventative approach to support individuals to modify their risk behaviours.

## Study status

The study started recruiting in September 2020.

## Data Availability

The anonymised participant datasets generated and/or analysed during the current study will be made available in the University of Malta institutional open access data repository https://www.um.edu.mt/library/oar/.

## Abbreviations

ASCVD: Atherosclerotic cardiovascular disease
CHD: Coronary heart disease
CVD: Cardiovascular diseases
LDL-c: Low-density lipoprotein cholesterol
MEDAS: Mediterranean diet adherence screener
RAPA: Rapid assessment of physical activity
CDC: Centres for Disease Control and Prevention
HLQ: Health literacy questionnaire
ACS: Acute coronary syndrome
COM-B: Capability Opportunity Motivation–Behaviour
